**LIST OF ABBREVIATIONS AND RELEVANT DEFINITIONS**

|                                  |                                                                                                                                      |
|----------------------------------|--------------------------------------------------------------------------------------------------------------------------------------|
| AE                        | Adverse Event                                                                                                                 |
| AR                        | Adverse Reaction                                                                                                              |
| BAT                       | Brown adipose tissue                                                                                                          |
| ADRB2                     | Beta-2-adrenergic receptor                                                                                                    |
| ADRB3                     | Beta-3-adrenergic receptor                                                                                                    |
| CCMO                      | Central Committee on Research Involving Human Subjects; in Dutch: Centrale Commissie Mensgebonden Onderzoek                   |
| ECG                       | Electrocardiogram                                                                                                             |
| EudraCT                   | European drug regulatory affairs Clinical Trials                                                                              |
| GCP                       | Good Clinical Practice                                                                                                        |
| IC                        | Informed Consent                                                                                                              |
| IV                        | Intravenous                                                                                                                   |
| IMP                       | Investigational Medicinal Product                                                                                             |
| IMPD                      | Investigational Medicinal Product Dossier                                                                                     |
| LUMC                      | Leiden University Medical Centre                                                                                              |
| (S)AE                     | (Serious) Adverse Event                                                                                                       |
| SPC                       | Summary of Product Characteristics; in Dutch: officiële productinformatie IB1-tekst                                           |
| SUSAR                     | Suspected Unexpected Serious Adverse Reaction                                                                                 |
| WAT                       | White adipose tissue                                                                                                          |
| F-FDG PET/CT | Glucose analogue, 2-[F]fluoro-2-deoxy-D-glucose positron emission tomography (PET)/computed tomography (CT) scan |

## SUMMARY

### Rationale:

The prevalence of obesity and associated metabolic diseases is increasing at a disturbing rate. Type 2 diabetes mellitus (T2DM) and cardiovascular diseases (CVD) are currently the leading cause of global death [2]. Obesity is the result of energy intake exceeding energy expenditure. An important contributor to energy metabolism and a promising target to counterbalance the positive energy balance in obesity is brown adipose tissue (BAT) [3]. BAT is a thermogenic organ that is able to combust triglyceride-derived fatty acids and glucose into heat [4, 5]. Naturally, the most well-acknowledged activator of BAT is cold exposure, which provokes an increased sympathetic outflow towards beta-adrenergic receptors on BAT [6, 7]. In rodents, the beta-3-adrenergic receptor (ADRB3) is predominantly found on brown and white adipocytes and activation of the ADRB3 has been shown to effectively activate BAT and improve (cardio)metabolic outcomes [8-10].

Although in humans the ADRB3 agonist mirabegron increases uptake of the positron-emitting glucose analogue 2- $^{18}\text{F}$ fluoro-2-deoxy-D-glucose ( $^{18}\text{F}$ FDG) by BAT, increases whole body lipolysis and increases resting energy expenditure, this only occurs after administration of a very high dosage of 200 mg [11], which highly exceeds the therapeutic dose to treat hyperactive bladder via ADRB3 activation (i.e. 50 mg). Since at 200 mg also cardiovascular side effects occur, mirabegron probably cross-reacts with ADRB1 and ADRB2 [12]. Furthermore, RNA sequencing analyses on human BAT showed, in contrast to mice, a negligible ADRB3 expression with a high ADRB2 expression. In vitro studies indeed indicate that ADRB2 is responsible activation of human BAT: 1) mirabegron increases oxygen consumption by human brown adipocytes that is inhibited by a specific ADRB2 antagonist, 2) the ADRB2 agonist formoterol activates oxygen consumption by human brown adipocytes, and 3) specific knock-down of ADRB2, and not ADRB1 or ADRB3, reduces oxygen consumption by human brown adipocytes[1]. Whether an ADRB2 agonist is able to activate human BAT *in vivo* has not been investigated yet, but the fact that several studies unequivocally show an increase in resting energy expenditure, lipolysis and lipid oxidation after intravenous (IV) administration of the ADRB2 agonist salbutamol is promising [13-15].

Everything considered, we hypothesize that sympathetic activation of human BAT is mainly mediated by the ADRB2 rather than the ADRB3.

**Objectives:**

1. To investigate the acute effect of ADRB2 activation, via intravenous administration of salbutamol (250 µg), on [F]FDG uptake by BAT.
2. To assess the acute effect of ADRB2 activation via intravenous administration of salbutamol (250 µg) on resting energy expenditure, serum markers for lipid- and glucose metabolism and plasma BAT markers.
3. To confirm that the stimulatory effect of salbutamol on [F]FDG uptake by BAT is not mediated via the ADRB3, by showing that the acute effect of i.v. salbutamol (250 µg) on BAT is blunted by co-administration of the ADRB1/2-blocker propranolol.

**Study design:**

The study is a randomized double-blinded cross-over trial, that will be carried out at the Leiden University Medical Center (LUMC). This trial encompasses one screening and two study days.

**Study population:**

This study will be carried out in 10 healthy white Caucasian males between 18 and 35 years old.

**Intervention:**

For all subjects on both study days the intervention consists of intravenous (IV) injection of salbutamol. This will be combined with either placebo (day 1 or 2) or propranolol (day 1 or 2) oral capsules, which will be given 60 minutes prior to salbutamol injection. In addition, to visualize supraclavicular BAT all subjects will undergo a dynamic [F]FDG PET/CT scan on both study days.

**Main study parameters/endpoints:**

- Glucose uptake by BAT, as measured by dynamic [F]FDG PET/CT acquisition
- Resting energy expenditure, as measured by indirect calorimetry
- Serum markers for lipid metabolism (triglycerides (TG), total cholesterol (TC), high density lipoprotein-cholesterol (HDL-C), low density lipoprotein cholesterol (LDL-C), free fatty acids)
- Lipid pathway analysis using lipidomic analysis in plasma samples
- Serum markers for glucose metabolism (glucose, insulin)
- Circulating plasma BAT markers (e.g. microRNAs)

**Nature and extent of the burden and risks associated with participation, benefit and group relatedness:**

This study consists of three study visits: one screening visit (~1 hour) and two study days (~3.5 hours per day). A total amount of 87.5 mL blood will be drawn, divided over the three visits. In addition, on both study days participants will undergo an [F]FDG PET/CT scan, with a radiation burden of 8.4 mSv in total. Prior to the PET/CT scan, on both study days

participants will receive 250 µg salbutamol via IV injection, either in combination with placebo or with 80 mg propranolol in capsules. Several pre-cautions regarding the IV administration of salbutamol will be taken into account to prevent from severe side-effects.

Subjects will not directly benefit from participation in this study. However, the results from this study are indispensable for unravelling the working mechanism of human BAT. In addition, the results from this study could reveal new therapeutic targets to activate human BAT and could therefore contribute to the fight against the worldwide obesity epidemic. Therefore, the risks of this study are considered defensible.

## 1. INTRODUCTION AND RATIONALE

### 1.1 Introduction

Globally, the prevalence of obesity and associated metabolic diseases is increasing at a disturbing rate, leading to an increased disability and mortality. Since 1975 the worldwide prevalence of obesity has virtually tripled and in 2016 13% of all adults were obese [16]. Importantly, obesity is one of the main risk factors for the development of type 2 diabetes mellitus (T2DM) and cardiovascular diseases (CVD), which are currently the leading causes of global death [2]. Obesity is the result of a disequilibrium between energy intake and energy expenditure. Treatment strategies focusing on decreasing energy intake via diet or increasing energy expenditure via physical exercise are not effective enough in long-term due to incompliance. Therefore, alternative stimulation of mechanisms involved in energy dissipation are a promising target for the treatment of obesity and consequently for the prevention of metabolic diseases.

### 1.2 Brown adipose tissue as target to treat and prevent cardiometabolic disease

Brown adipose tissue (BAT) has recently come forth as an important factor in energy metabolism. BAT is a highly vascularized thermogenic organ mainly located in the neck region, along the large vessels and in the supraclavicular area. BAT consists of numerous small lipid droplets and a high number of mitochondria. Through the presence of uncoupling protein-1 (UCP-1) in the inner mitochondrial membrane, BAT is able to combust triglyceride-derived fatty acids and glucose into heat and is therewith involved in a process known as thermogenesis [4]. Naturally, the most well-acknowledged activator of BAT is cold exposure. Via cold-sensing receptors in the skin several hypothalamic nuclei in the brain are stimulated, subsequently leading to the release of noradrenalin from sympathetic neurons that binds to adrenergic receptors present on brown adipocytes [6, 7]. Short term cold exposure is known to increase uptake of glucose and fatty acids by BAT, which with an concurrent increase in intracellular release of fatty acids leads to enhanced oxidative energy metabolism in human [17]. Long term cold exposure has been shown to increase energy expenditure and reduce fat mass [18, 19]. Thus, activation of BAT is considered a promising target to counterbalance the positive energy balance provoking obesity and associated cardiometabolic diseases [3]. However, since cold exposure is not a supreme tool for prevention and treatment, alternative targets for activating human BAT are highly demanded. A logical purpose would be to directly stimulate the adrenergic receptors on BAT, to pharmacologically mimic cold exposure.

### 1.3 Rodents: *ADRB3* dominant in activating BAT

In rodents, the beta-3-adrenergic receptor (*ADRB3*) is predominantly found on brown and white adipocytes[10]. Directly targeting the *ADRB3* has been shown to effectively activate

BAT and improve metabolic outcomes [8, 9]. More specifically, activation of the ADRB3 reduces body weight, reduces plasma triglyceride and cholesterol levels, and as a result attenuates atherosclerosis development [8]. Until recently, it was generally assumed that the ADRB3 would also be the most important activating receptor on human BAT.

#### 1.4 Humans: ADRB2 dominant in activating BAT?

Several human studies have in turn aimed to investigate the effect of directly targeting the ADRB3 using mirabegron. The ADRB3 agonist mirabegron is currently approved for the treatment of overactive bladder in a therapeutic dose of 50 mg per day. At the maximal allowable dose, mirabegron (200 mg) indeed increases [ $^{18}\text{F}$ ]FDG uptake by BAT, whole body lipolysis and resting energy expenditure compared to placebo [11]. However, at this dose mirabegron also evokes cardiovascular side effects, such as increases in heart rate (HR) and diastolic and systolic blood pressure (BP). These findings suggest that mirabegron (200 mg) not only stimulated the ADRB3, but also the ADRB1 and possibly ADRB2 that are present on the heart and cardiovascular system [12]. More recent studies investigating the administration of a therapeutic dose (50 mg) of mirabegron show variable results. One study does show an increase of glucose uptake by BAT, albeit to a significantly lower extent compared to the 200 mg dose ( $18 \text{ mL} \cdot \text{SUV}_{\text{mean}} \cdot \text{g/mL}$  versus  $306 \text{ mL} \cdot \text{SUV}_{\text{mean}} \cdot \text{g/mL}$ ,  $P = 0.007$ ) [20]. Another recent study found no effect of the 50 mg dose on glucose uptake by BAT, nor on BAT oxidative metabolism or BAT blood flow[1].

[figure not shown]

Figure 1 [ $^{18}\text{F}$ ]FDG uptake on PET/CT scan after administration of placebo, 50 mg mirabegron and 200 mg mirabegron.  
Baskin et al. *Diabetes* (2018) [15]

Altogether, this led to the hypothesis that high dose mirabegron activates BAT through cross-reaction with ADRB1 and/or 2, rather than activating ADRB3. Indeed, we recently showed by RNA sequencing a negligible expression of ADRB3 in human BAT, with abundant expression of ADRB2. In vitro studies indeed indicate that ADRB2 is responsible activation of human BAT: 1) mirabegron increases oxygen consumption by

human brown adipocytes that is inhibited by a specific ADRB2 antagonist, 2) the ADRB2 agonist formoterol activates oxygen consumption by human brown adipocytes, and 3) specific knock-down of ADRB2, and not ADRB1 or ADRB3, reduces oxygen consumption by human brown adipocytes[1]. Whether ADRB2 agonism is indeed able to activate human BAT *in vivo* has not been investigated yet, but the fact that several studies do show an increase in resting energy expenditure, lipolysis and lipid oxidation after intravenous (IV) administration of the ADRB2 agonist salbutamol is promising [13-15].

[figure not shown]

Figure 2 Oxygen consumption rate of *in vitro* differentiated human brown adipocytes on baseline (Basal), after the addition of formoterol, mirabegron and noradrenaline (Stimulation), leak (Leak) and chemically uncoupled respiration (Maximal). Brown adipocytes were pre-incubated without and with the  $\beta_2$ -AR antagonist ICI 118,551. Data are mean  $\pm$  SEM of  $n = 4$ . Blondin et al.[1].

### 1.5 Visualization of human BAT

The most commonly used method to visualize human BAT *in vivo* is the use of a static positron emission tomography (PET)/computed tomography (CT) scan, with the positron emitting glucose analogue 2- $^{18}\text{F}$ fluoro-2-deoxy-D-glucose ( $^{18}\text{F}$ FDG) as a tracer. The  $^{18}\text{F}$ FDG tracer is taken up by the sodium-independent glucose transport family (GLUT1, GLUT3 and GLUT4) by metabolically active tissues, amongst which BAT, and can be visualized on PET. The CT scan in turn provides the anatomical reference and distinguishes tissues according to their radiodensity. While many investigators apply static whole-body scans to provide a precise measurement of relative integrated uptake of this tracer between tissues, few have used the dynamic  $^{18}\text{F}$ FDG PET acquisition to precisely determine quantitative measures of BAT glucose uptake rates [21, 22]. Applying a dynamic approach for image acquisition, allows for the derivation of image-acquired, tissue-specific, time-radioactivity curves to determine: fractional tissue-specific glucose extraction ( $K_t$ , in  $\text{min}^{-1}$ ), net tissue-specific glucose uptake ( $K_m$ , in  $\text{nmol}\cdot\text{g}^{-1}\cdot\text{min}^{-1}$ ) or if needed the relative integrated uptake of  $^{18}\text{F}$ FDG by the tissue within the period of acquisition (as a static scan would). The fractional glucose extraction and net glucose

uptake rate provide important pharmacokinetic information about the tissue-specific transport of glucose ( $K_t$ ) and the net uptake of glucose in response to the drug over time. SUV allows for a comparison of the cumulative uptake of glucose between tissues over a fixed period of time. Therefore, dynamic [ $^{18}\text{F}$ ]FDG PET/CT acquisition provides a quantitative and highly sensitive (picomolar range) method to study the effect of a compound on glucose metabolism of human BAT.

### **1.6 Hypothesis and aims**

Everything considered, we hypothesize that sympathetic activation of human BAT is mediated by the ADRB2 rather than the ADRB3.

In this study we aim to investigate the effect of stimulation of the ADRB2 with salbutamol (250  $\mu\text{g}$ ) on BAT fractional glucose extraction and net glucose uptake rate by dynamic PET/CT with [ $^{18}\text{F}$ ]FDG. In addition, we aim to show that this effect is abolished when the ADRB1 and 2 are blocked and that this effect is thus not mediated by cross-reaction of salbutamol with the ADRB3. Furthermore, the effect of stimulation of the ADRB2 on resting energy expenditure, plasma lipid and glucose concentrations and plasma BAT markers will be assessed.

## OBJECTIVES

### Primary Objective:

1. To investigate the acute effect of ADRB2 activation, via intravenous administration of salbutamol (250 µg), on [F]FDG uptake by BAT.

### Secondary Objectives:

2. To assess the acute effect of ADRB2 activation via intravenous administration of salbutamol (250 µg) on resting energy expenditure, serum markers for lipid- and glucose metabolism and plasma BAT markers.
3. To confirm that the stimulatory effect of I.V. salbutamol (250 µg) on [F]FDG uptake by BAT is not mediated by the ADRB3, by showing that the acute effects of ADRB2 activation by salbutamol is blunted when propranolol (ADRB1/2-blocker) is co-administered.

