#### *Propranolol and placebo*

During the two study days administration of our investigational product salbutamol will be preceded with either placebo (study day A) or 80 mg propranolol (study day B), given orally divided over two capsules (Figure 3 and 4). Propranolol is a non-selective ADRB1/2 blocker, approved and commonly used in clinical care for the treatment of hypertension, secondary prophylaxis after a myocardial infarction, angina pectoris, hypertrophic obstructive cardiomyopathy, arrhythmias, thyrotoxicosis and as prophylaxis for migraine [36]. In literature the use of propranolol is regarded to be effective to suppress BAT in patients undergoing an [ $^{18}\text{F}$ ]FDG PET/CT for oncology reasons [37-40]. Propranolol administered in a dosage of 80 mg orally two hours before [ $^{18}\text{F}$ ]FDG PET/CT acquisition was shown to almost completely suppress BAT activity [40]. This same method is also mentioned in the guidelines for tumor imaging from the European Association of Nuclear Medicine [41].

In this study, propranolol will be used to reverse activation of BAT after administration of salbutamol by antagonizing its effect on the ADRB1 and B2. The ultimate goal is to show that the effect of salbutamol on BAT is hereupon abolished and thus not mediated via overspill towards the ADRB3.

For a summary of findings from non-clinical and clinical studies regarding pharmacological safety of propranolol we refer to the Summary of Product Characteristics (SPC), which can be found on the website of the 'College ter Beoordeling van Geneesmiddelen' (CBG) (<https://www.geneesmiddeleninformatiebank.nl/nl/>, registration numbers RVG 12638) and to the product specification in appendix D2.

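### Objective 3 takes blunting by propranolol as proof that salbutamol's effect is not ADRB3-mediated, while Sections 1.6 and 6.1 require abolition, which the planned difference test cannot show

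*Protocol*

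**What the plan says.** Objective 3 appears in the Summary and again under Secondary Objectives. Its conclusion and its evidence stand in one sentence. The conclusion is that the ADRB3 does not mediate the uptake effect of salbutamol. The evidence for it is that this effect "is blunted when propranolol (ADRB1/2-blocker) is co-administered". No size of reduction is required.

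Two other places ask for more. Section 1.6 aims to show that "this effect is abolished when the ADRB1 and 2 are blocked". Section 6.1 (Propranolol and placebo) gives as the ultimate goal that the "effect of salbutamol on BAT is hereupon abolished and thus not mediated via overspill towards the ADRB3". The sample size in Section 3.4 also assumes a complete fall, from 22 nmol/g/min to the thermoneutral level of 9.

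On design, the Summary states: "For all subjects on both study days the intervention consists of intravenous (IV) injection of salbutamol". The days differ only in placebo versus propranolol, and there is no scan without salbutamol. Sections 9 and 9.1 plan a two-condition test of difference (a paired t-test or a rank test). They give no criterion for how much uptake may remain under propranolol.

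**The concern.** The protocol uses two standards for one conclusion, and the formal objective carries the weaker one. On the protocol's own description, propranolol blocks ADRB1 and ADRB2. Any salbutamol effect that survives it is therefore where an ADRB3 component would lie. Blunting shows that part of the effect needs ADRB1/2. It says nothing about what mediates the rest.

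At stake is the mechanistic conclusion. As Objective 3 is worded, a significant difference with a material remainder could be read as confirming that the ADRB3 plays no part. The primary comparison itself is unaffected.

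**Working it through.** **Inputs (Section 3.4).** 22 ± 14 nmol/g/min from the study of 200 mg mirabegron; 9 ± 4 from the thermoneutral study; difference 13; SD 10, taken as the SD of the within-subject difference; alpha 0.01; power 80%; n = 10. Sidedness is not stated, so two-sided is assumed.

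**1. Reproducing the plan's n.** n = [(t(0.995, n−1) + t(0.80, n−1)) × SD / difference]².
- From n = 10: [(3.250 + 0.883) × 10/13]² = 10.1.
- From n = 11: [(3.169 + 0.879) × 10/13]² = 9.7.

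The iteration settles between 9.7 and 10.1, so the stated 10 is reproduced on a two-sided reading. The exact noncentral t gives 77.7% power at n = 10.

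**2. Smallest significant difference.** t(0.995, 9) × SD/√n = 3.250 × 10/√10 = 3.250 × 3.162 = 10.3, which is 79% of 13. The remainder is 13 − 10.3 = 2.7, and 2.7/13 = 21%. If the placebo-day mean were 22, the propranolol-day mean would be 11.7, not 9.

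**3. How often partial blockade is significant** (noncentral t, n = 10, SD 10, two-sided alpha 0.01):

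| True blunting of an effect of 13 | True difference | Probability of significance |
|---|---|---|
| 50% | 6.5 | 19% |
| 75% | 9.75 | 48% |
| 100% | 13 | 78% |

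**4. A larger salbutamol effect.** Section 3.4 expects an effect at least as big as that of high-dose mirabegron. Assume 26 for illustration. Blunting of 50% is then a true difference of 13, significant with probability 78%, while 13 nmol/g/min stays unblocked. At the bare threshold, 26 − 10.3 = 15.7 would remain, about 60%.

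**5. What the difference contains.** Let B be uptake without salbutamol and S the salbutamol effect, with B′ and S′ the same under propranolol. The between-day difference is (B + S) − (B′ + S′) = (S − S′) + (B − B′). Abolition means S′ = 0. The two scans give only B + S and B′ + S′, so S′ is not identified. Section 6.1 itself reports that propranolol almost completely suppressed BAT activity in clinical PET patients, so B′ may lie below B. A propranolol-day mean of 9 would then still allow S′ = 9 − B′ > 0.

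**6. What an interval on the propranolol day can add.** The SD on that day is not given. Assume a range from 4 (thermoneutral) to 14 (mirabegron).
- The 95% half-width is 2.262 × 4/3.162 = 2.9 at SD 4, and 2.262 × 14/3.162 = 10.0 at SD 14.
- At SD 4, a mean of 9 gives 6.1 to 11.9, and the threshold mean of 11.7 gives about 8.9 to 14.6, which still includes 9.

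The interval describes the remainder. It cannot certify abolition.

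**The case against.** The best defence is that abolition is the protocol's declared goal and its planning assumption, that *blunted* is loose drafting in a secondary objective, and that no decision rule equates a significant p-value with absence of the ADRB3. An analysis plan that is not shown may also fix the interpretation. Part of this stands: the overstatement lies in the objective's wording, not in a formal rule. But the objective itself states both the evidence and the conclusion, and no analysis plan can make the first imply the second. Reading *not mediated* as *not wholly mediated* would rescue the inference, but Sections 1.6 and 6.1 plainly mean more than that.

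The defence is also right that the numbers are moderate. The only alpha in the protocol is 0.01. A reader might use 0.05 and obtain a larger remainder, but the protocol states no such level. At 0.01, halving an effect of 13 would usually not reach significance.

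A stronger reading is tempting: that the trial fails because propranolol does not separate ADRB1 from ADRB2, while Section 1.6 says "we hypothesize that sympathetic activation of human BAT is mediated by the ADRB2 rather than the ADRB3". The documents do not support this as a fault in Objective 3, which concludes only about the ADRB3. For that question, blocking ADRB1 and ADRB2 together is coherent. The remark in Section 1.4 that "high dose mirabegron activates BAT through cross-reaction with ADRB1 and/or 2" concerns mirabegron, not salbutamol. The protocol rests ADRB2 over ADRB1 on salbutamol's selectivity (Sections 4.1 and 12.1) and on the knock-down data (Section 1.4), not on the propranolol day. A third scan in each subject would also bring the radiation dose to 3 × 4.2 = 12.6 mSv, above the 10 mSv threshold the protocol observes.

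**Conclusion.** The point holds for the ADRB3 inference. Objective 3 draws a conclusion that blunting cannot support, other sections apply a different standard, and the planned test cannot demonstrate the stricter one. This follows from the design and does not depend on the planning figures.

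The size does depend on them: about 21% of the assumed effect unblocked at the significance threshold, given an effect of 13, an observed SD of 10, n = 10 and two-sided alpha 0.01. It is a threshold case, not the expected result. A larger salbutamol effect or a smaller SD raises it, and a larger SD lowers it. For example, SDs of 14 and 4 with an assumed between-day correlation of 0.5 give √(196 + 16 − 56) = 12.5 for the difference. The threshold is then 3.250 × 12.5/3.162 = 12.8, and the remainder about 1%.

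**What to change.** - Use one criterion in the Summary objectives, Secondary Objectives, Section 1.6 and Section 6.1.
- State that a significant placebo–propranolol difference shows BAT glucose uptake under salbutamol to be at least partly ADRB1/2-dependent. Remove absence of ADRB3 mediation as the conclusion.
- Report the propranolol-day mean with its confidence interval beside the thermoneutral value of 9. Label the comparison as external and descriptive, with no pass mark.
- State that, without a salbutamol-free scan and with propranolol itself suppressing BAT, this comparison cannot establish complete blockade of the salbutamol effect.

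No new arm, scan or subject is needed. The cost is some rewording, one interval and a more modest mechanistic claim.
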